### Sample size {14}

The sample size calculation is based on the Swedish average incidence of NEC and mortality in extremely preterm infants, which is comparable for Denmark. During the first two to three postnatal days before the intervention is started, the mortality rate is highest among extremely preterm infants. We will calculate the mortality rate from the start of the third postnatal day, as this is the estimated time the enrolled infants will be exposed to the intervention. Based on pooled incidence rate data from SNQ data from the years of 2019, 2020, and 2021, we considered an 18% base rate of the composite outcome NEC and/or mortality, with an estimated 9% overlap. We estimated a 30% reduction, as this was considered clinically relevant and was also the NEC risk reduction rate seen in the ProPrems trial [6]. After analyzing the relative risk for the power analysis, assuming a significance level of 0.05 and 30% reduction rate with interim analysis based on a Pocock boundary at 1/3, 2/3s, and 100% of the information, the proposed enrollment of 1620 patients will have sufficient power [7] to test our hypotheses. Patient enrollment will continue until this number has been reached. Assuming an 80% consent rate, we expect to enroll 1620 infants in 3 years and 8 months.

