#### Primary aim 1 and secondary aims 1–3

In the initial analysis, we will compare baseline characteristics of the study population between allocation groups to ensure that balance was achieved by the randomization. We will report the mean (standard deviation [SD]) or median (first quartile, third quartile) for continuous variables, and count and percentages for categorical variables. The primary analyses will be based on the ITT population including all subjects that were randomized in the study. A crude and a multivariable-adjusted standardized logistic regression will be used to calculate the relative risk (RR) and 95% CI to estimate the effect of probiotic supplementation on the risk of NEC and/or mortality (primary aim) as well as NEC, total mortality, and LOS separately (secondary aims 1–3). The randomization will be stratified per site. Thus, the analysis will adjust for this variable before standardization. A per-protocol analysis accounting for non-compliance will also be performed. All data analyses will be performed using the STATA and R software. A two-sided *p*-value of 0.05 will be considered significant evidence of the effect of the intervention.

#### Secondary aims 4 and 5

The effect of probiotic supplementation on the rate of prescription and duration of antibiotic use during hospital stay (secondary aim 4) and duration of hospital stay (secondary aim 5) will be analyzed using standardized logistic regression and linear regression model.

#### Secondary aim 6

The effect of probiotic supplementation on gut microbiome will be investigated by comparing the alpha and beta diversity of the microbiota samples. Alpha diversity measures the mean diversity within a sample while beta diversity involves a comparison of diversities between samples and will be displayed as a principal coordinate or component analysis plot.

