### Interim analyses {21b}

The DSMC will carry out interim analysis based on a Pocock boundary for safety and efficacy analyses at the time points when 1/3 (*n*=540), 2/3 (*n*=1080), and 3/3 (*n*=1620) of patients have been included. All interim analyses will use the same method as described for primary aims and secondary aims 1-3. A two-sided *p*-value of 0.02205 will be considered significant evidence of the effect of the intervention for the first interim analysis, 0.3794 for the second, and 0.05 at full information accrual.

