### Composition of the data monitoring committee, its role and reporting structure {21a}

A DSMC was established consisting of two experienced clinicians with expertise in neonatology and research methodology and one biostatistician. All cases of SAEs, SUSARs, and other AEs that clinicians deem concerning and report will be reviewed by the committee. Criteria for stopping the ongoing intervention will be decided by the committee. Information about how SUSARs are reported is described in paragraph below.

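### The three stated significance cut-offs are cumulative Pocock alpha, not per-look p-values; even with the evident misprint corrected, overall two-sided type I error is about 8%, not 5%

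*Protocol article*

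**What the plan says.** - **Sample size {14}** works at an overall level, "assuming a significance level of 0.05 and 30% reduction rate", and plans "with interim analysis based on a Pocock boundary at 1/3, 2/3s, and 100% of the information". The base rate of the composite is 18%, the total is 1620, and power is called sufficient without a figure.
- **Interim analyses {21b}** states the purpose: "The DSMC will carry out interim analysis based on a Pocock boundary for safety and efficacy analyses at the time points" when 540, 1080 and 1620 infants have been enrolled. It then gives the two-sided p-values that count as significant evidence of effect: 0.02205 "for the first interim analysis, 0.3794 for the second, and 0.05 at full information accrual".
- **Statistical methods {20a}, Primary aim 1 and secondary aims 1–3**, gives the main analysis a two-sided p-value "of 0.05 will be considered significant evidence of the effect of the intervention", with no allowance for the earlier looks.

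The article nowhere calls the three values cumulative alpha. The sentence makes each of them the cut-off for the p-value at its own look.

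**The concern.** A Pocock boundary is defined by equal nominal significance levels at all looks, the last included. Cut-offs that rise from look to look therefore contradict the design named in the same section. A final cut-off equal to the full 0.05 leaves nothing to pay for the two earlier tests.

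At stake is the trial's main claim. The article expects its result to inform guidelines. As written, a final result with p between 0.02205 and 0.05 would be declared significant although the design named in the article does not support it, and the overall error rate would exceed the 0.05 on which the trial was sized.

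**Working it through.** **Inputs.** Overall two-sided alpha 0.05; Pocock boundary; information fractions t = 1/3, 2/3, 1; control rate 18%; 30% relative reduction, so 0.18 × 0.70 = 12.6%; 1:1 allocation, so 810 per arm; total 1620 (Sample size {14}, Trial design {8}). Cut-offs 0.02205, 0.3794, 0.05 (Interim analyses {21b}). Assumed, because not stated: 80% power.

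**1. The plan's sample size.** The fixed-design total is 2 × (1.960 + 0.842)² × (0.18 × 0.82 + 0.126 × 0.874) / 0.054² ≈ 1387 with unpooled variance, and 1394 with pooled variance. The three-look Pocock inflation factor at 80% power is 1.166. This gives 1387 × 1.166 ≈ 1618 and 1394 × 1.166 ≈ 1626, so 1620 is reproduced. At 85% or 90% power the total would be about 1847 or 2145, which does not match.

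**2. The correct boundary.** Under the null, the test statistics at the three looks are jointly normal with correlation √(tᵢ/tⱼ). Solve for the constant c in

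1 − P(|Z₁| < c, |Z₂| < c, |Z₃| < c) = 0.05.

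The result is c = 2.2895, a nominal two-sided p of 0.02205 at each look. The cumulative alpha spent is 0.02205, 0.03794 and 0.05000.

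**3. Origin of the printed values.** These are the printed digits, with 0.03794 appearing as 0.3794. The Lan–DeMets Pocock-type spending function gives cumulative 0.02264, 0.03817 and 0.05, which does not match. The values are therefore the cumulative alpha of the classical Pocock boundary.

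**4. Overall type I error when the values serve as per-look cut-offs.** This is 1 − P(|Z₁| < c₁, |Z₂| < c₂, |Z₃| < c₃), with cₖ the two-sided normal quantile of each cut-off. It was found by recursive numerical integration and confirmed by simulation. The last column counts trials whose first crossing favours probiotics, which by symmetry is half.

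| Cut-offs at looks 1 / 2 / final | Cumulative two-sided error | Overall | Favouring probiotics |
|---|---|---|---|
| 0.02205 / 0.3794 / 0.05 (as printed) | 0.022, 0.381, 0.384 | 38.4% | about 19% |
| 0.02205 / 0.03794 / 0.05 (decimal corrected) | 0.022, 0.052, 0.080 | 8.0% | about 4.0% |
| 0.02205 / 0.02205 / 0.05 (only the final 0.05 kept) | 0.022, 0.038, 0.072 | 7.2% | about 3.6% |
| 0.02205 at all three looks (Pocock) | 0.022, 0.038, 0.050 | 5.0% | 2.5% |

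The third row shows that the final 0.05 accounts for most of the excess.

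**5. What this means at the final analysis.** With 810 per arm and an observed control rate of 18%, the crude log relative risk has SE = √[0.82/(810 × 0.18) + (1 − p₂)/(810 × p₂)].
- At p₂ = 0.144: SE = 0.114, and exp(−1.960 × 0.114) ≈ 0.80.
- At p₂ = 0.138: SE = 0.115, and exp(−2.2895 × 0.115) ≈ 0.77.

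An observed relative risk between about 0.77 and 0.80 would be called significant under the plan but not under the boundary it names.

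**6. Power.** With 1620 infants and 0.02205 at every look, power is 79.1% to 80.0%, depending on the variance formula. With the decimal-corrected cut-offs it would be about 87%; the difference comes from the extra type I error.

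**The case against.** Several objections are fair and limit the point.

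- **The 38% rests on a misprint.** A second value of 0.3794 between 0.02205 and 0.05 is evidently 0.03794, and a committee with a biostatistician is unlikely to apply it. This stands: 38.4% is what the sentence says, not what the trial would probably do. But 8.0% remains after the correction.
- **A statistician would recognise the values as cumulative alpha.** Perhaps, but nothing in the text says so, and the final 0.05 appears again in the main statistical section as the ordinary significance rule. An analysis plan not shown would not cure cut-offs stated wrongly here.
- **The rates count crossings in both directions.** Correct. The error in favour of probiotics is half: about 4.0% against 2.5% intended.
- **A crossing is not a stop.** Correct. The cut-offs define significant evidence, and "Criteria for stopping the ongoing intervention will be decided by the committee". A reader might infer that wrong early stopping is likely; the text does not support that. Leaving stopping criteria to the committee is ordinary in a condensed article. It does not repair the published cut-offs, the final one least of all.

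Two further inferences go beyond the documents.

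- **Incomplete outcomes.** Looks are triggered by inclusion while death is counted to 40 weeks (Table 1), so one might conclude that many infants lack an outcome at every look. For the final look the article specifies full information. Under Reporting serious adverse events it requires these events, which include NEC and death, to be documented within two weeks of the end of each infant's intervention, so that interim analyses can be done. Deaths between 34 and 40 weeks are not covered by that rule, so at the interims a clarification is warranted, not more.
- **Four outcomes on one boundary.** The sentence "of patients have been included. All interim analyses will use the same method as described for primary aims and secondary aims 1-3" could be read as letting NEC, mortality or sepsis alone cross the boundary. It speaks of method only, and the aims rank the composite as primary. Any figure for the extra error would rest on correlations that the article does not give.

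**Conclusion.** The cut-offs are wrong as written and must be changed. They are the cumulative alpha of a three-look Pocock design presented as per-look p-value cut-offs, one with a misplaced decimal. The realistic size of the error is an overall two-sided type I error of about 8.0% instead of 5%; the literal reading gives 38.4%. These rates assume looks at exactly 1/3, 2/3 and all of the information, and count a crossing at any look, in either direction, as a positive finding, as Interim analyses {21b} words it. Multiplicity across secondary outcomes and detailed stopping rules may properly sit in the analysis plan or the committee's charter and form no part of this conclusion.

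**What to change.** - In Interim analyses {21b} and in the section on primary aim 1 and secondary aims 1–3, state that the primary composite is significant only if two-sided p < 0.02205 (|Z| > 2.2895) at look 1, look 2 and the final analysis. Remove 0.3794, and remove the final 0.05 for that outcome. If the cumulative alpha is to be shown as well, label it as such: 0.02205, 0.03794, 0.05.
- As a minor clarification, state that the boundary governs the primary composite only. Base each interim look on infants with a complete primary outcome (death or 40 weeks), because Sample size {14} sets the looks on information while Interim analyses {21b} triggers them on inclusion.
- State the power for which 1620 was calculated.

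**Cost.** Wording in the protocol, the analysis plan and the committee's documents, and a stricter final test (0.02205 instead of 0.05). The sample size need not change: 1620 agrees with the correct boundary at an assumed 80% power. If the interims wait for complete outcomes, they fall somewhat later than the inclusion trigger.

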### Methods for additional analyses (e.g., subgroup analyses) {20b}

All primary, secondary, and tertiary outcomes alongside baseline characteristics and potential covariates are described above in section Outcomes {12} and Table 1 and Table 3. We will perform a sensitivity analysis for variables, including but not limited to sex, site, gestational age, birth weight, and mode of delivery.

Subgroup analyses for site, sex, and gestational age will be performed, the latter consisting of both infants born between 22 weeks + 0 days to 24 weeks + 6 days and those born between 25 weeks + 0 days to 27 weeks + 6 days.

For the sub-cohort, we will perform subgroup analyses based on type of enteral nutrition (volumes of breastmilk intake) and amount of macro- and micronutrients in relation to growth, body composition, and enteral feeding tolerance. The cut-off value for macro- and micronutrient intake will be based on ESPGHAN’s recommendation for parenteral and enteral intake (below recommended intake, in line with recommendation, or above recommended intake) [48].

Additional subgroup analyses may be performed if empirical data show unexpected patterns, such as potentially systematical differences in baseline characteristics, outcome, or adverse events (AE) between groups. All planned subgroup analyses will clearly be stated in the study report.

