### Outcomes {12}

Table 1 (complete cohort) and 2 (sub-cohort) include descriptions of primary, secondary, and other outcomes including analysis metric, method of aggregation and time points for outcome collection in the PEPS trial. Details of NEC and LOS will be collected for validation of diagnoses and understanding of disease events. Serious adverse events (SAE) will be collected for interim analysis. All covariates collected in the trial are relevant for analyzing the risk of developing the primary and secondary outcomes and will primarily be used for sensitivity analysis.

**Table 1 Tab1:** Description of outcomes with analysis metric, aggregation method, and time points in main cohort

Outcome variables complete cohort			
*Primary outcome variables*	*Analysis metrics*	*Method of aggregation*	*Time point*
Necrotizing enterocolitis	Incidence rate	Mean/Median	During study intervention (until 34 weeks of gestational age)
Necrotizing enterocolitis Bell Stage >II^a^ Verified	Incidence rate	Mean/Median	During study intervention (until 34 weeks of gestational age)
Necrotizing enterocolitis Bell Stage >III^a^ Verified	Incidence rate	Mean/Median	During study intervention (until 34 weeks of gestational age)
Necrotizing enterocolitis Operation	Date, time	Mean/Median	During study intervention (until 34 weeks of gestational age)
Abdominal symptoms	Incidence of free gas, intermural intestinal gas, inflated abdomen discolored abdomen, stagnant intestinal loop >24 h	Sum	During study intervention (until 34 weeks of gestational age)
Differential gastrointestinal diagnoses	Spontaneous intestinal perforation, Malrotation/volvulus, other	Sum	During study intervention (until 34 weeks of gestational age)
X-ray of the abdomen	Incidence rate	Mean/Median	During study intervention (until 34 weeks of gestational age)
Death	Incidence rate	Mean/Median	Third day postpartum until 40 weeks of gestational age

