***Characteristics/covariates***			
Pregnancies	Number	Mean/Median	Baseline
Preeclampsia	Yes/No	Mean/Median	Baseline
Chorioamnionitis	Yes/No	Mean/Median	Baseline
Infection pregnancy	Number of infections	Sum	Baseline
Antibiotics during pregnancy	Period	Sum	Baseline
Mode of delivery	Vaginal or Cesarean-section	Mean/Median	Baseline
Apgar-score	At 1, 5 and 10 minutes	Mean/Median, Sum	Baseline
Gender (x/y)	Boy/girl	Mean/Median	Baseline
Multiple birth	Yes/No	Mean/Median	Baseline
Gestational age	Number (gestation week)	Mean/Median	Baseline
Birth weight	Kilograms	Mean/Median	Baseline
Birth length	Centimeters	Mean/Median	Baseline
Birth head circumference	Centimeters	Mean/Median	Baseline
Z-scores from growth chart at birth	Reference Niklasson [73] and Fenton [74]	Standard deviation	Baseline
Respiratory support Intubation	Period of treatment	Mean/Median	From birth until 40 weeks of gestational age
Respiratory support Continuous positive airway pressure (CPAP)	Period of treatment	Mean/Median	From birth until 40 weeks of gestational age
Respiratory support High-flow nasal cannula	Period of treatment	Mean/Median	From birth until 40 weeks of gestational age
Respiratory support Low-flow nasal cannula	Period of treatment	Mean/Median	From birth until 40 weeks of gestational age
Patent ductus arteriosus closure strategies Paracetamol	Period of treatment	Mean/Median	From birth until 40 weeks of gestational age
Patent ductus arteriosus closure strategies Operation	Date	Mean/Median, Sum	From birth until 40 weeks of gestational age

^a^See definition of Bell Stage >II-III under “Plans for assessment and collection of outcomes {18a}”

^b^See definition of verified late-onset sepsis under “Plans for assessment and collection of outcomes {18a}”

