## Assignment of interventions: allocation

### Sequence generation {16a}

Randomization will be done within 24 h after written consent has been obtained from the legal guardians. Allocation to either intervention or control group will be made using the randomization software, *Randomize.net*. The randomization will be stratified by center and the patient will be allocated to either group C or group D.

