#### Data collection and assessment for sub-cohort

Data on postnatal growth (Table 3) during the intervention period will be registered as per clinical routine in the nutritional calculation software, Nutrium (nutrium.se). All growth data from the intervention period will be retrieved from Nutrium. Growth data during long-term follow-up will be collected from SNQ and/or medical records (sub-cohort).

**Table 3 Tab3:** Description of outcomes with analysis metric, aggregation method, and time points in sub-cohort

Outcome variables sub cohort			
*Outcome variables - feeding tolerance*	*Analysis metrics*	*Method of aggregation*	*Time point*
Enteral nutrition	Number of days until full enteral feeds	Mean/Median	During study intervention (until 34 weeks of gestational age)
Parental nutrition	Number of days with parental nutrition	Mean/Median	During study intervention (until 34 weeks of gestational age)
Interruptions of enteral nutrition	Number of enteral nutrition interruptions >8 h	Mean/Median	During study intervention (until 34 weeks of gestational age)
Enteral nutrition decreased due to clinical instability	Number of EN decrease >50%	Mean/Median	During study intervention (until 34 weeks of gestational age)
Use of breastmilk fortifiers	Number of days until breastmilk fortifiers is induced	Mean/Median	During study intervention (until 34 weeks of gestational age)
Feeding tube requirement	Number of days requiring a feeding tube	Mean/Median	During study intervention and until 40 weeks of gestational age
Macronutrient intake	Amount of macronutrients given (kcal/kg/day)	Mean/Median	During study intervention (until 34 weeks of gestational age)
Micronutrient intake	Amount of micronutrients given (μg or mg/kg/day)	Mean/Median	During study intervention (until 34 weeks of gestational age)

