***Characteristics/covariates***			
Use of medical steroids	Period of treatment	Mean/Median	From birth until 5.5 years of age
Use of tetracyclines	Period of treatment	Mean/Median	From birth until 5.5 years of age
Type of enteral nutrition mothers’ own milk, donated breastmilk, formula	Percentages (%)	Proportion	During study intervention (until 34 weeks of gestational age)
Breastmilk fortification	Type	Proportion	During study intervention (until 34 weeks of gestational age)
Breastfeeding at discharge	Full, partly, none	Proportion	Discharge from neonatal intensive care unit/homecare

Daily nutritional assessment of enteral and parenteral nutrition during the intervention period will be documented in Nutrium. These assessments include all macro- and micronutrient intake including type, amount, and strategy of enteral and parenteral feeds. Data on breastmilk fortification and interruptions of enteral feeds will also be documented and collected from Nutrium.

Assessment of body composition will be made at 3 months corrected age using air displacement plethysmography (PeaPod). This is considered “the gold standard” for measuring body composition, including fat, fat-free mass, and bone density, for infants weighing below 8 kg [72]. It applies whole-body plethysmography which is a fast, reliable, and non-invasive assessment. Assessment of body composition will be documented and retrieved from patient records.

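### Sub-cohort subgroups are defined by nutrient and breast-milk intake measured after randomisation, so arm comparisons within them can be biased

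*Protocol article*

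**What the plan says.** All references are to the protocol article.

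- **Methods for additional analyses {20b}** commits, for the sub-cohort, to this: "we will perform subgroup analyses based on type of enteral nutrition (volumes of breastmilk intake) and amount of macro- and micronutrients". The outcomes are growth, body composition and enteral feeding tolerance. Nutrient intake is cut against a published recommendation into three levels: "below recommended intake, in line with recommendation, or above recommended intake".
- **Table 3, feeding-tolerance outcomes**, contains the same nutrient variables, measured during the intervention up to 34 weeks: "Amount of macronutrients given (kcal/kg/day" and "Amount of micronutrients given (μg or mg/kg/day" (both entries close with a bracket).
- **Table 3, characteristics/covariates**, contains type of enteral nutrition (own milk, "donated breastmilk, formula"). It covers the same window but is not listed as an outcome.
- **Sequence generation {16a}** fixes the timing: "Randomization will be done within 24 h after written consent has been obtained from the legal guardians". Informed consent {26a} requires consent within 72 h of birth.
- **Probiotics and feeding tolerance** (last paragraph) lists nutritional intake among the things to be studied in relation to the probiotic.

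**The concern.** A subgroup analysis of a randomised trial keeps the protection of randomisation only if subgroup membership cannot depend on the assigned arm. Here the plan groups infants by something that it also treats as a possible effect of the product.

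Suppose the probiotic raises intake. An infant on placebo who reaches a given intake level did so without that help and is, on average, less ill than an infant on probiotic at the same level. Less ill infants also grow better. The two arms within a stratum are then no longer comparable, and a difference in growth can appear where there is none.

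For feeding tolerance the plan is also close to circular. Days to full feeds, interruptions and feed reductions help to determine intake, and intake then defines the strata in which tolerance is examined.

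At stake is how the sub-cohort results are read. The Discussion presents body composition in relation to nutritional intake as one of the trial's contributions, so these strata are likely to be reported.

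**Working it through.** The plan gives no figure for these analyses, so there is none to reproduce. The check has two parts.

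**1. Is the grouping variable post-randomisation?** Consent is due by 72 h and randomisation within 24 h of it, so randomisation comes at latest 72 + 24 = 96 h, or 4 days, after birth. From birth to 34 weeks + 0 days is 12 weeks = 84 days for an infant born at 22 + 0, and 6 weeks + 1 day = 43 days for one born at 27 + 6. At most 4 of 43 to 84 days can precede randomisation, and Table 3 counts intake during the intervention. The achieved intake is therefore post-randomisation in practice.

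**2. How large can the distortion be?** The document supplies none of the quantities needed, so all of the following are assumptions. Let A be the arm (1 = probiotic), U an unmeasured health factor, M intake and Y growth, the latter two in SD units:

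- M = d·A + ρ·U + √(1 − ρ²)·e₁
- Y = ρ·U + √(1 − ρ²)·e₂, so that the true effect of A on Y is zero

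Here d is the shift in intake caused by the probiotic, and ρ² is the share of the variance of intake and of growth that is due to U. Intake is cut at ±0.43 SD into three strata. With 4 million simulated infants, the probiotic-minus-placebo differences in Y are:

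| d | ρ (ρ²) | Low | Middle | High |
|---|---|---|---|---|
| 0.2 | 0.3 (0.09) | -0.016 | -0.017 | -0.012 |
| 0.2 | 0.5 (0.25) | -0.033 | -0.048 | -0.032 |
| 0.2 | 0.7 (0.49) | -0.072 | -0.094 | -0.067 |
| 0.5 | 0.3 (0.09) | -0.032 | -0.042 | -0.031 |
| 0.5 | 0.5 (0.25) | -0.092 | -0.119 | -0.082 |
| 0.5 | 0.7 (0.49) | -0.184 | -0.231 | -0.164 |

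With d = 0, every stratum lies between -0.004 and 0.001, which is simulation noise. The unstratified difference lies between -0.001 and 0.002 in every setting.

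**Cross-check by formula.** Within an arm, Var(M) = 1 and Cov(M, Y) = ρ², so E(Y | A, M) = ρ²(M − d·A). At a fixed intake the spurious arm difference is therefore −d·ρ². For d = 0.2 and ρ = 0.3 this is −0.2 × 0.09 = −0.018 (regression on the simulated data: -0.019). For d = 0.5 and ρ = 0.7 it is −0.5 × 0.49 = −0.245 (simulated: -0.245). The three-level strata give slightly smaller values because they hold intake less tightly fixed.

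**The case against.** Several points can fairly be made on the other side.

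- **Arm comparisons are not spelled out.** The section speaks of intake subgroups in relation to growth, body composition and tolerance, which could mean an association between intake and outcome. That reading is possible. But the analyses are called subgroup analyses and follow directly on the treatment-effect subgroups by site, sex and gestational age, so an arm contrast is a natural reading. The wording should settle it.
- **The shift in intake may be small.** The cut-offs refer to parenteral as well as enteral intake. If total intake is classified, parenteral supply may offset poor enteral tolerance. This stands. It lowers d and also weakens the circularity for tolerance.
- **These are tertiary aims at one hospital.** This also stands and limits the weight of the point.

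A reader might infer more than the documents support:

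- *That breast-milk intake is also an outcome in Table 3.* Type of enteral nutrition is listed there as a covariate. It is post-randomisation, but it is not an outcome reused as a stratifier.
- *That the plan adjusts the main outcomes for later treatments.* Outcomes {12} does say that "All covariates collected in the trial are relevant for analyzing the risk of developing the primary and secondary outcomes", and Table 1's covariate block includes respiratory support and treatment of the ductus arteriosus recorded "From birth until 40 weeks of gestational age". But these covariates are meant primarily for sensitivity analysis, all five sensitivity variables named in {20b} are baseline variables, and only site is named for adjustment in the main model. The open wording permits such adjustment without committing to it, and the covariate set is detail commonly left to the analysis plan.
- *That a real growth benefit would appear as harm.* The simulation sets the true effect to zero. A benefit would change sign only if it were smaller than the bias, and that was not examined.

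**Conclusion.** The point holds in a limited form. The protocol commits to sub-cohort subgroups on intakes measured after randomisation, and nutrient intake is at once an outcome and a stratifier. Probiotic-placebo comparisons within those strata can be biased; it does not follow that they will be.

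Two conditions are needed: the probiotic must shift intake, and intake must share causes with growth or tolerance. The second is plausible on the protocol's own account, since its section on feeding tolerance ties intolerance to suspected illness, withheld feeds and growth restriction. The first is what the trial is meant to find out.

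Under the assumed model the size runs from zero with no shift to about -0.01 to -0.23 SD for shifts of 0.2 to 0.5 SD. Neither the shift nor the strength of the shared cause can be taken from the document, so this range shows the mechanism and does not predict this trial's result. The intention-to-treat analysis of the primary composite is not affected, nor is the unstratified arm comparison in the sub-cohort.

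**What to change.** In {20b}, for the sub-cohort:

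1. Analyse macro- and micronutrient intake by arm as outcomes, as Table 3 already lists them.
2. Form treatment-effect subgroups only on baseline variables already collected, for example gestational age (with the two bands defined for the complete cohort), sex or birth-size z-score.
3. If analyses by nutrient intake or breast-milk volume are kept, label them as exploratory association or mediation analyses, and state that they are not treatment-effect subgroups.

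This is a change of wording. It needs no new data and leaves the sample size alone. The loss is that an intuitive split by achieved intake can no longer be presented as a treatment-effect subgroup; it can still be shown descriptively.
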